### Study timeline

In order to meet recruitment targets and maximise the interval between immunisation and the final OPS within the structure of the school exam year, the study will recruit across 4 ‘waves’ over 20 months: wave 1 March–May 2018; wave 2 September–November 2018; wave 3 March–May 2019; wave 4 September–November 2019 (figure 2). The academic teaching year runs from September until April or May, depending on local jurisdictions. Recruitment will be balanced between study groups for each of the ‘Spring’ (March–May) and ‘Autumn’ (September–November) recruiting periods in view of expected seasonal variation in carriage. Completion of the final post-vaccination pharyngeal swab collection is expected in early 2021.

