### Randomisation, allocation and blinding

This is an open-label partially randomised study, with group allocation by study site. All schools within the geographical coverage area of each study site will be allocated to the same study arm, both for logistical reasons and because geographical allocation may increase the potential to detect any impact on herd protection. As a post-licensure study, blinded administration and/or placebo will not impact on the outcome of carriage prevalence and would introduce unnecessary cost and complexity to a trial of this scale. The allocation of initial sites was determined prior to the start of the study (figure 1). A capacity assessment stratified sites to either the control arm or immunisation sites depending on existing site expertise and the requirements to maintain equal numbers in each study arm. The immunisation sites were randomised to either the MenB-fHbp Group or the 4CMenB Group. Additional sites may be added during the study and will be pragmatically allocated to a study group to ensure balanced recruitment.

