### Interventions

All participants will be required to attend three study visits at their school (figure 3). Following informed consent, a baseline OPS will be taken by study staff using a standardised method of collection. A flocked swab will be used to sweep from one tonsil across the posterior pharynx to the contralateral tonsil. Participants in all groups will complete a brief questionnaire collecting demographic data and risk factors for meningococcal carriage such as smoking and antimicrobial use (see online supplemental file).^23^ The questionnaire is compatible with previous large-scale UK meningococcal carriage studies conducted in 1999, 2000, 2001 and 2014–2015, and the B Part of It Australian Study, which will allow an assessment of risk factors over time.^11 19 24 25^ The 4CMenB and MenB-fHbp groups will both receive a two-dose vaccine schedule at 0 and 6 months and all groups will have a second OPS taken at 12 months following enrolment. The Control Group will be offered a two-dose schedule of 4CMenB vaccination after their second OPS. Individual swab results will not be given to participants, in accordance with previous meningococcal carriage studies, however participants will be contacted confidentially if *N. gonorrhoeae* is detected.

10.1136/bmjopen-2020-037358.supp1Supplementary data

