### Statistical methods

A baseline analysis will occur after wave 2 when the study reaches approximately 50% enrolment. This descriptive analysis of baseline carriage rates will assess the validity of the prospective sample size calculation. There will be no interim analysis of vaccine impact. The principal analysis will be conducted using a modified intention to treat approach, including all participants who have had two throat swabs. Participants will be analysed according to allocated group, regardless of vaccine receipt. Based on previous UK school-based meningococcal carriage studies, the design effect was assumed to be 1.5 in the sample size calculations but will be calculated on the actual data collected.^24 25^

For the primary objective and each of the secondary objectives, carriage rates will be expressed as a mean with two-sided 95% Clopper-Pearson CIs for each group at baseline and at 12 months. The carriage rates in the MenB-fHbp and 4CMenB groups will be compared separately to the Control Group. The OR with two-sided 95% CIs will be calculated using logistic regression via a generalised estimating equations model using an exchangeable working correlation structure. Model covariates will include age, gender, season of recruitment and baseline carriage status a priori. Additional risk factors found to affect carriage at baseline will also be included. Gender and smoking (smoking, home smoking and vaping) are known to affect both vaccine-induced immune responses and meningococcal carriage, and these interactions will be reported regardless of significance. The level of statistical significance will be 0.05. There will be no imputation of missing data for the principal analysis.

Sensitivity analyses will be done for the primary and each of the secondary objectives and will include: analyses without adjustment or inclusion of covariates for completeness and to confirm the results from the primary analyses; a per-protocol analysis of participants who received both vaccine doses in the 4CMenB and MenB-fHbp groups; adjustment for the month of the outcome measure rather than season of recruitment to further investigate the potential effect of seasonality and multivariable imputation for missing data. All variables that will be included in the analysis model will be included in the imputation model and will assume data are missing at random.

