The short follow-up period of between 6 and 9 months following the second vaccination is a limitation of this study, reducing the ability to observe any potential impact during later periods of high-acquisition risk, for example, when commencing tertiary education.^32^ The large sample size required and mobility of school-leavers limit the feasibility of ongoing carriage surveillance. The secondary endpoint assessing the impact on other *Neisseria* spp. is based on those present in the oropharynx and culturable on selective media, however all swabs and products of culture will be stored for potential further analysis.

Due for completion in 2021, The ‘Be on the TEAM’ Study will directly inform international MenB immunisation policy. It will contribute to an open-access repository of *Neisseria* spp. genomes and provide a biobank of samples to assist in identifying strategies for future MenB vaccine development.

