### Current study progress

At the time of writing 24 048 participants have been enrolled from over 120 schools across the UK. Assemblies raising awareness about meningitis, immunisation and research have reached over 40 000 students. In March 2020, study visits were temporarily suspended due to the SARS-CoV-2 pandemic and at this time, 11 170 participants had successfully completed the study. The protocol may require modifications to fulfil the study objectives.

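### The primary model's only time covariate, season of recruitment, pools 2018 with 2019 recruits and so mainly pre- with post-suspension swabs; recruitment wave would guard against calendar-time bias at almost no cost

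*Protocol article*

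**What the plan says.** The primary analysis is a logistic model fitted by generalised estimating equations, comparing each vaccine arm with control. On covariates, Statistical methods states: "Model covariates will include age, gender, season of recruitment and baseline carriage status a priori". Risk factors found to affect carriage at baseline are to be added. A sensitivity analysis replaces season of recruitment by month of the outcome swab, with seasonality as its stated purpose.

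Study timeline gives the recruitment calendar as "wave 1 March–May 2018; wave 2 September–November 2018; wave 3 March–May 2019; wave 4 September–November 2019". It also says "Recruitment will be balanced between study groups for each of the" spring and autumn recruiting periods, because carriage is expected to vary by season. Under Interventions, "all groups will have a second OPS taken at 12 months following enrolment". Study timeline adds: "Completion of the final post-vaccination pharyngeal swab collection is expected in early 2021".

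Current study progress reports that in March 2020 "study visits were temporarily suspended due to the SARS-CoV-2 pandemic". By then 24 048 had been enrolled and 11 170 had completed. The same section says that the protocol may need modification.

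The section on randomisation and allocation says that all schools in a site's area share one arm. Control sites were separated from immunisation sites by a capacity assessment, and only the immunisation sites were randomised, between the two vaccines. It continues: "Additional sites may be added during the study and will be pragmatically allocated to a study group to ensure balanced recruitment".

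**The concern.** The article names two recruiting seasons over four waves. The natural coding of season therefore has two levels: spring (waves 1 and 3) and autumn (waves 2 and 4). Each level joins recruits of two calendar years whose outcome swabs fall on either side of the March 2020 suspension. The model has no term that separates them.

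The other covariates do not fill the gap. By the stated calendar every baseline swab was due by November 2019. Neither baseline carriage nor a risk factor selected at baseline can absorb a change in carriage that arises in 2020.

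In an individually randomised trial this would cost little, because arms would be balanced over time by design. Here allocation is by region, with 16 regions, and the vaccine-versus-control contrast is not randomised. A regional difference in when swabs are completed is therefore a potential arm difference. If carriage also moved between the periods, calendar time would be confounded with vaccine group in the primary comparison.

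**Working it through.** **1. The plan's own figure.** Inputs from Sample size: 8000 per arm, retention 80%, design effect 1.5, control carriage 3.43%, a 30% reduction (to 2.40%), significance level 0.05, taken as two-sided.

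- Effective n per arm = 8000 × 0.80 / 1.5 = 4267.
- Power for 3.43% against 2.40% = 80.7%.

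The stated 80% reproduces and is not in dispute.

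**2. When outcome swabs fall due** (enrolment plus 12 months)

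| Season level | Earlier wave: swab due | Later wave: swab due |
|---|---|---|
| Spring | wave 1: March–May 2019 | wave 3: March–May 2020 |
| Autumn | wave 2: September–November 2019 | wave 4: September–November 2020 |

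The article does not break the 11 170 completers down by wave, so the match between wave and period is an inference from the calendar.

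**3. Share of late swabs**

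- Completed at suspension: 11 170 / 24 048 = 46% of those enrolled.
- Expected swabs at 80% retention: 24 048 × 0.80 = 19 238.
- Remaining after suspension: 19 238 − 11 170 = 8068, which is 42% of 19 238.

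**4. Bias if no period term is used.** Let qc and qv be the late-swab shares in the control and vaccine arms, and r the ratio of later to earlier carriage. With no true vaccine effect,

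spurious RR = [1 − qv(1 − r)] / [1 − qc(1 − r)].

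The article gives none of the three quantities; all are assumptions. With r = 0.5:

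- 10-point gap, 40% against 50% late: 0.75 / 0.80 = 0.94.
- 10-point gap, 50% against 60% late: 0.70 / 0.75 = 0.93.
- 20-point gap, 35% against 55% late: 0.725 / 0.825 = 0.88.
- 20-point gap, 40% against 60% late: 0.70 / 0.80 = 0.875.

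The table gives the range as an odds ratio, taking 3.43% as the earlier carriage. In brackets is the chance of a significant result with no true effect (normal approximation, effective n 4267 per arm).

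| r | Equal shares, 42% | 40% control, 50% vaccine | 35% control, 55% vaccine |
|---|---|---|---|
| 0.75 | 1.00 (5.0%) | 0.97 (5.6%) | 0.94 (7.5%) |
| 0.50 | 1.00 (5.0%) | 0.94 (7.8%) | 0.88 (16.6%) |
| 0.25 | 1.00 (5.0%) | 0.89 (12.5%) | 0.79 (35.8%) |

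Swapping the arms inverts the ratio. For r = 0.5, 1/0.94 = 1.07 and 1/0.88 = 1.14, which would hide a real benefit.

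**5. With a period term.** Within a period both arms have the same carriage in this set-up, so the odds ratio is 1.00 in every cell. A wave term achieves this as far as wave tracks period.

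**6. Scale.** A spurious RR of 0.875 is ln(0.875)/ln(0.70) = 37% of the targeted 30% reduction on the log scale.

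**The case against.** The strongest reply has four parts.

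*Balance is promised.* Recruitment is to be balanced between groups for each recruiting period, which can be read as every wave, and added sites are to be allocated with balance in mind. With balance over calendar time the bias is nil. This stands as a real safeguard, but it concerns enrolment. It does not ensure that completed 12-month swabs stay balanced after an interruption.

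*The plan predates the event.* Version 5.0 is dated 24 January 2020, and the article says that modifications may follow. This stands too: the absence of a suspension term is no oversight. Pooling 2018 with 2019 recruits, however, is a choice already in the model, and no remedy is named.

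*A sensitivity analysis exists.* Adjustment for month of swab would help if coded as month and year. The coding is not stated and the declared aim is seasonality. It also leaves the primary estimate as it is.

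*The size is hypothetical.* This is correct. The article shows neither a change in carriage nor an arm imbalance.

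Some stronger readings are tempting but unsupported. A reader might infer that waves 1 and 2 were complete at suspension, that sites had been added, or that visits would restart site by site. The article gives only a total, says only that sites may be added, and does not describe the restart. A reader might also see a contradiction between the nominal 6 months after the second dose and the Discussion's wording, "The short follow-up period of between 6 and 9 months following the second vaccination is a limitation of this study". That fits a visit window, and the article refers to a figure, not reproduced here, for the window ranges.

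**Conclusion.** The point holds as a weakness of a stated model term. It is not evidence that the trial's estimate is biased. Season of recruitment, read as two levels, cannot separate calendar years, and the remaining primary covariates cannot stand in for it. About 42% of expected swabs would fall after the suspension at the planned retention.

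Bias needs two things together: a change in carriage between periods and a difference between arms in the share of late swabs. Neither is shown. If later carriage is halved, a gap of 10 to 20 points gives a spurious RR of about 0.93 to 0.88, or the reverse. The effect is smaller with a milder change in carriage and zero with balance. The allocation method makes an imbalance possible, which is reason enough to protect the primary estimate when protection is this cheap.

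A reader might go on to conclude that only pre-suspension swabs should carry the main result. The article does not require that. With 11 170 / 3 / 1.5 = 2482 effective participants per arm, assuming equal arms, power would be about 58%, so making that subset a key analysis would be a preference.

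**What to change.** - In the primary model, replace season of recruitment by recruitment wave with four levels. Wave contains season, separates the years, and is fixed at enrolment, so vaccination cannot affect it.
- Tabulate completed 12-month swabs by arm and calendar period, so that readers can see whether the arms are balanced.
- Code the month-of-outcome sensitivity analysis as month and year, or add an indicator for swab before or after March 2020, and report the vaccine effect by period.

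Time from enrolment to swab need not enter the primary model, because it arises after allocation.

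The cost is a few model terms. Only wave and swab dates are needed, and no participant is lost from the analysis. The article plans no interim analysis of vaccine impact, so the change can be written down before any effect estimate is seen. If the arms prove balanced over time, little is given up.

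### The only missing-data sensitivity analysis shares the complete-case analysis's assumption, so agreement between them would not show robustness to dropout related to carriage

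*Protocol article*

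**What the plan says.** All of this is in the protocol article, Statistical methods, unless stated otherwise.

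- Principal analysis set: a "modified intention to treat approach, including all participants who have had two throat swabs", analysed by allocated group.
- Missing data in that analysis: "There will be no imputation of missing data for the principal analysis".
- Model: logistic GEE with an exchangeable working correlation. On covariates: "Model covariates will include age, gender, season of recruitment and baseline carriage status a priori". Also: "Additional risk factors found to affect carriage at baseline will also be included".
- Missing-data sensitivity analysis: "multivariable imputation for missing data", specified as follows: "All variables that will be included in the analysis model will be included in the imputation model and will assume data are missing at random".
- The other sensitivity analyses are an unadjusted analysis, a per-protocol analysis and adjustment for month of outcome. None addresses missing swabs.
- Sample size assumes 80% retention, so 20% loss is planned.
- Interventions: "The Control Group will be offered a two-dose schedule of 4CMenB vaccination after their second OPS". Vaccinees are scheduled to have had both doses by month 6.
- Current study progress: 24 048 were enrolled, and 11 170 had completed when visits were suspended in March 2020.

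**The concern.** A missing-data sensitivity analysis should be able to give a different answer when the principal analysis is biased by dropout. The one described has little scope to do so. If the 12-month swab is missing and missingness depends only on arm and the model covariates, the adjusted complete-case regression is already valid. Imputing the outcome from those same variables under the same assumption adds Monte Carlo noise but no information. If missingness depends on carriage itself, or on something outside the model, both analyses carry the same bias.

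This trial has reasons to want a sharper check. It is open-label with allocation by region. Controls are offered vaccine only after the final swab, so the incentive to return may differ by arm. The article itself describes school-leavers as mobile. Loss may also exceed plan after the suspension: 24 048 − 11 170 = 12 878 participants had not completed at that point, although they were pending and not necessarily lost. With control carriage assumed at 3.43%, a modest excess among non-returners in one arm moves the odds ratio noticeably. Close agreement between the two planned analyses could then be reported as robustness that was never tested.

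**Working it through.** **1. The plan's own figures.** Control carriage p_C = 0.0343; a 30% reduction gives p_V = 0.7 × 0.0343 = 0.02401. With two-sided 0.05 and 80% power, the pooled two-proportion formula gives 4196 per arm. Then 4196 × 1.5 / 0.80 = 7868, against the stated 8000. The sample size reproduces and is not in dispute. The planned odds ratio is (0.02401/0.97599) / (0.0343/0.9657) = 0.02460 / 0.03552 = 0.693.

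**2. Does imputation from the same variables depart from complete-case?** Simulation: 2 × 8000 participants, 60 replicates, 20 imputations, adjusted logistic models without clustering. The missingness mechanisms are assumptions.

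| Missingness of the 12-month outcome | Missing | Full-data OR | Complete-case | Imputed, same variables | Imputed, factor added |
|---|---|---|---|---|---|
| Depends on model covariates | 21% | 0.684 | 0.682 | 0.682 | 0.681 |
| Depends on carriage, vaccine arm only | 18% | 0.689 | 0.533 | 0.535 | 0.533 |
| Depends on a factor outside the model, vaccine arm only | 13% | 0.693 | 0.640 | 0.641 | 0.697 |

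In the first row the standard error of the log odds ratio is 0.123 for both planned analyses. The mean absolute difference between their log odds ratios is at most 0.009 in every row. In the second row both carry the same bias. In the third, adding the responsible factor removes the bias; in the other two rows that factor is unrelated to outcome and missingness.

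**3. Size at the protocol's rates.** Let m be the fraction unswabbed and k the ratio of carriage odds in unswabbed to swabbed participants. For an arm with observed rate p:

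q = k·p/(1−p) / [1 + k·p/(1−p)], and all-participant rate = (1−m)·p + m·q.

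Vaccine arm, m = 0.20, k = 2: q = 0.04920/1.04920 = 0.04689. The rate is 0.8 × 0.02401 + 0.2 × 0.04689 = 0.02859, with odds 0.02943. With controls unshifted, OR = 0.02943/0.03552 = 0.829.

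| Loss, both arms | k vaccine | k control | OR, all participants |
|---|---|---|---|
| 20% | 1 | 1 | 0.693 |
| 20% | 1.5 | 1 | 0.761 |
| 20% | 2 | 1 | 0.829 |
| 20% | 0.5 | 1 | 0.623 |
| 20% | 1 | 2 | 0.580 |
| 20% | 2 | 2 | 0.694 |
| 40% | 1.5 | 1 | 0.830 |
| 40% | 2 | 1 | 0.966 |

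The multipliers and the 40% loss are assumptions. The direction can go either way. When the relation is the same in both arms and loss is equal, the odds ratio barely moves.

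**4. Against the planned precision.** Effective n per arm = 8000 × 0.80 / 1.5 = 4267. SE of the log odds ratio = √[1/(4267 × 0.0343 × 0.9657) + 1/(4267 × 0.02401 × 0.97599)] = √(0.00708 + 0.01000) = 0.131. Holding that SE fixed as an approximation, |ln OR|/SE is 2.81 at 0.693, 2.09 at 0.761 and 1.44 at 0.829. A result exactly on plan would therefore lose significance somewhere between k = 1.5 and k = 2 in the vaccine arm alone.

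**5. Unequal loss without an arm-specific relation.** With 17% loss in controls, 22% in vaccinees and non-returners carrying at twice the rate in both arms (all assumed), the risk ratio is 0.7 × 1.22/1.17 = 0.730, that is, 27% in place of 30%. This is a small shift. The larger biases need dropout to relate to carriage differently by arm.

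**The case against.** The strongest reply is that the sentence sets a minimum. Including every analysis-model variable is the standard compatibility requirement, and nothing excludes auxiliary variables. The third simulation row shows that one well-chosen addition can make imputation depart from complete-case and correct it. The text also speaks of missing data generally. If questionnaire items or baseline carriage are imputed, participants otherwise dropped return to the analysis and the estimate can change. This stands. A reader might infer that the two analyses must agree by construction, but the document supports only an expectation of close agreement for missing 12-month swabs with the variables named.

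A reader might also infer that the imputation ignores region and school. The article is silent on this, so it cannot be called an error.

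On attrition, the document gives a retention assumption of 80% and no observed loss. Reading it as a floor of 20% missing is unsupported, and no arm-specific rate is given. The prize draw for everyone completing the final swabbing visit and the option of community follow-up for school-leavers both work against differential loss.

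Last, it can be said that such detail belongs in the full protocol or SAP, which are not shown. That does not dispose of the point. The article does not leave the matter open: it fixes the analysis set, the mechanism assumed and the required content of the imputation model, and among the sensitivity analyses it lists none relaxes the mechanism.

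**Conclusion.** The point holds in a limited form. As described, the sole missing-data sensitivity analysis is imputation under missing at random, with no variables named beyond the analysis model. For missing 12-month swabs it is expected to track the adjusted complete-case result, and agreement would say nothing about dropout related to carriage.

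The possible size depends on assumed multipliers. At 20% loss in both arms, 1.5 to 2 times the carriage odds in unswabbed vaccinees only would move the planned odds ratio from 0.69 to 0.76–0.83. A common relation with equal loss produces almost no change. The documents show neither that such dropout occurred nor its direction. A reader should not conclude that the trial's estimate is biased, only that the stated plan would not reveal it if it were. The plan should be strengthened here; the point does not invalidate the principal analysis.

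**What to change.** 1. Add an arm-specific delta-adjusted (tipping-point) analysis of the primary outcome. For example, set the odds of carriage in non-returners at 0.5 to 2 times those in returners, varied separately in each vaccine group and in controls. Report where the conclusion changes.
2. Extend the missing-at-random imputation with auxiliary variables that are already collected and lie outside the analysis model. Examples are recruitment wave and whether the final visit fell before or after the suspension, doses received (within the vaccine groups), baseline carriage of other *Neisseria*, and questionnaire items not selected as covariates.
3. State that the imputation respects the clustering used in the GEE.
4. Report 12-month swab completion by arm, so that the delta range can be judged against actual loss.

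The cost is some extra analysis time and no new data. The ranges and auxiliary variables should be fixed before the outcome data are analysed.
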